## Abstract

**Background:**

Cognitive impairment and cerebrovascular pathology are both frequent with ageing. Cognitive impairment due to vascular pathology of the brain, termed vascular cognitive impairment (VCI), is one of the most frequent causes of cognitive impairment in elderly subjects. Thus far, VCI has no specific pharmacological treatment. Recent observational studies have suggested a protective effect of physical activity in cognition, but adequate randomised controlled trials (RCT) are lacking.

**Methods:**

AFIVASC is a multi-centre randomised controlled trial, with a 6-month intervention treatment and an additional follow-up of 6 months, that aims to estimate the impact of 6 months of moderate intensity physical activity on cognition (the primary outcome) at 6 and 12 months in subjects with VCI. Participants are community dwellers with criteria for VCI without dementia or who have had previous stroke or transient ischaemic attack (TIA). Patients may be self-referred or referred from a medical appointment. After confirming the inclusion criteria, a run-in period of 1 month is conducted to access adherence; only after that are subjects randomly assigned (using a computerised program blinded to clinical details) to two groups (intervention group and best practice usual care group). The intervention consists of three physical activity sessions of 60 min each (two supervised and one unsupervised) per week. The primary outcome is measured by the presence or absence of decline in cognitive status. Secondary outcomes include changes in neuro-cognitive measures, quality of life, and functional and motor status. Primary and secondary outcomes are evaluated at 6 and 12 months by investigators blinded to both intervention and randomisation. A required sample size of 280 subjects was estimated. Statistical analyses will include regression analysis with repeated measures. The study was approved by the Ethics Committee for Health of Centro Hospitalar de Lisboa Norte (ref. no. 1063/13) and by the Ethics Committee for Health of Centro Hospitalar do Porto CHP (ref. no. 2016.055(049-DEFI/048-CES)).

**Discussion:**

We aim to show whether or not moderate physical activity has a beneficial impact on cognition, quality of life, motor, and functional status in people with vascular cognitive impairment, and to generate new insights on the applicability of implementing physical activity in this specific population.

**Trial Registration:**

ClinicalTrials.gov, NCT03578614 July 6, 2018.

**Electronic supplementary material:**

The online version of this article (10.1186/s13063-019-3174-1) contains supplementary material, which is available to authorized users.

## Background

Cognitive impairment is frequently associated with ageing, and cerebral vascular pathology is one of its most frequent causes [1, 2]. Vascular cognitive impairment (VCI) includes a myriad of clinical conditions having cerebrovascular aetiology in common that ultimately leads to some degree of cognitive impairment. Cognitive impairment ranges from single domain impairment, behavioural changes and mild multi-domain impairments to dementia (the most severe stage, termed vascular dementia). Dementia is characterised by a compromise of several cognitive domains that leads to functional decline (either in the social, occupational or personal and family context) and loss in autonomy in performing activities of daily living of different complexity. In milder forms, cognitive impairment due to vascular aetiology can be difficult to diagnose since it may be expressed by symptoms which tend to be linked to ageing and not to memory impairment. Examples of these symptoms are reduced verbal or motor initiative, psychomotor slowness, difficulty in multi-tasking, difficulty in planning, sequencing and finalizing actions, or even behavioural manifestations only (shown as less interest in hobbies or usual activities, and irritability or distractibility). VCI is caused by a heterogeneous group of vessel disorders causing different types of vascular lesions in the brain, from subclinical small vessel disease (including white matter changes, lacunes, or microbleeds) to clinically overt stroke [1, 2].

There is no specific treatment for VCI, and pharmacological trials have thus far generated negative results [3, 4]. Therefore, in the absence of a cure, efforts should be made to improve research and intervention in vascular risk factors [4–6]. Physical activity has gained increasing interest as a non-pharmacological treatment for both primary prevention and for delaying evolution in cognitive impairments due to vascular disease. In animal studies, physical activity has been shown to produce several metabolic effects (increased expression of neurotransmitters, increased hippocampal cell proliferation and neurogenesis, increased antioxidant capacity, reduced inflammatory cytokines and oxidative stress, and improved mitochondrial functioning and vascular endothelial function), leading to better neuroplasticity [7]. In human functional and cerebral perfusion studies, physical activity was also associated with improvement in brain functioning [8].

The World Health Organization (WHO) (2010) [9] and the American College of Sports Medicine (2017) [10] have produced recommendations on physical activity. The associations of cardiovascular [11] and cerebrovascular diseases [12] also produced recommendations on physical activity for cardiac and for stroke patients, respectively. However, data on cognitive disorders are quite controversial. Recent observational studies suggested that physical activity could prevent the progression of VCI [13]. On the other hand, a recent review found no protective effect of physical activity in cognitive decline [14]. In the DAPA trial published recently, no beneficial effect was achieved with physical activity in patients with Alzheimer’s disease [15]. There have been intervention trials in patients at high vascular risk without previous stroke but, with the exception of one study [16] (which did not include VCI), no benefit was found [17, 18].

Given these contradictory findings, we lack a robust evidence base to recommend physical activity in VCI. Furthermore, there are no data on what type, intensity, and frequency of activity would be necessary to achieve long-term gains.

We aim to test, through a randomised controlled trial (RCT), if physical activity has a beneficial impact on VCI. We hypothesise that regular physical activity of moderate intensity for at least 6 months will improve cognitive impairment in subjects with cognitive impairment due to cerebrovascular pathology.

We also aim to evaluate the effect of physical activity on the quality of life, and on functional and motor status.

## Objectives

The primary objective is to conduct an RCT to evaluate the effect of 6 months of physical activity on cognitive performance in subjects with VCI without criteria of dementia at inclusion. We aim to evaluate cognitive performance (as the primary outcome), and quality of life and motor performance and functional status (as secondary outcomes). Other objectives are to identify the determinants for the progression of cognitive decline and quality of life in a large Portuguese sample of subjects with VCI without dementia and also to evaluate the impact of the engagement in physical activities in both subjects and informants.

## Methods/design

### Design

AFIVASC (“physical activity in vascular cognitive impairment’) is a Portuguese multi-centre, randomised parallel group trial comparing a 6-month intervention of two moderate physical activity sessions and one unsupervised moderate physical activity session per week with an additional follow-up of 6 months to evaluate its long-term impact in comparison with the current best practice usual care. The Consolidated Standards of Reporting Trials (CONSORT) statement [19] has been used as a framework for the development of our methodology (Fig. 1). To ensure adherence, a run-in period will be conducted after inclusion. This run-in period consists of a 4-week period before randomisation during which all participants are assigned to equal procedures, namely the educational session and all planned assessments. After the run-in period, participants are randomised into two parallel groups (best practice usual care group and the intervention group). The best practice usual care group will receive the standard usual care, but they are allowed to perform physical activity by self-initiative, although supervised physical intervention is not allowed. The control of the amount of physical activity per week is performed in both groups through accelerometry. We do not expect to see high levels of physical activity in the usual care group since VCI is usually associated with a reduced initiative.

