### Participants

#### Recruitment and study setting

The study is conducted in the University of Lisbon at the Faculdade de Medicina and Instituto de Medicina Molecular in Lisbon, and the Hospital de Santo António, Centro Hospitalar do Porto. The Human Kinetics Faculty (from the University of Lisbon) is a partner of the study. These centres, both urban and academic, have experience in the diagnosis and management of patients with cognitive decline of a vascular aetiology and in stroke care. Subjects are referred to each participating centre directly from the community (participants can be self-presenting, as the study was advertised in public spaces) or from a medical appointment (general family doctor in primary care, or from neurological, mental health, memory clinics, or hospital settings). Participants can be referred to the study due to minor cognitive complaints/symptoms or minor behavioural changes attributed to a cerebrovascular aetiology. Patients can also be referred if they had a previous stroke or transient ischemic attack (TIA), even without complaints, if neuropsychological evaluation showed evidence of any change considered to be due to a cerebrovascular aetiology. Post-stroke cognitive impairment is common even after successful clinical recovery from a stroke episode, and a recent study showed that at least one cognitive domain was impaired in 83% of cases [20]. Considering TIA, more than one cognitive domain was impaired in more than a third of patients 3 months after a TIA [21].

Eligible subjects are contacted by the recruitment team to further explain the procedures of the study and to confirm inclusion and exclusion criteria. Written informed consent is given by participants and informants. This consent allows access to the subject’s clinical records for research purposes and indicates their willingness to participate in all the activities inherent to the study. Those remaining eligible and without contraindications to physical activity are contacted by an investigator and proceed to baseline assessments.

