### Inclusion and exclusion criteria

#### Inclusion criteria

Participants are included if they are 18 years and older and fulfil the following criteria: 1) provide written informed consent; 2) are fluent in the Portuguese language; 3) are able to read and write; 4) have an available, reliable informant; and 5) show clinical and functional criteria A and B as below.

Criteria A (any one of the following three):Probable mild cognitive vascular impairment (VCI, no dementia) [22];Previous ischaemic or haemorrhagic stroke (more than 6 months before), with modified Rankin score ≤ 2 at baseline and without formal indication for physiotherapy;TIA (more than 1 month before), diagnosed by a neurologist or with an identified vascular lesion (correlated with TIA clinical symptoms) in cerebral computed tomography (CT)/magnetic resonance imaging (MRI).

Criteria B: No functional changes, i.e. instrumental activity of daily living (IADL) scale = 0 (no item changed, or one single item with minimal change), according to the scoring methods of the LADIS study (minimum of four items applicable) [23] or no cognitive changes regarding the suggested Montreal Cognitive Assessment Test (MoCA) cut-off point for dementia in Portuguese clinical samples (score < 17) [24].

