#### Exclusion criteria

Subjects cannot be included if they have at least one of the following: 1) a diagnosis of dementia; 2) stroke with formal indication for physiotherapy or speech therapy, or Rankin score ≥ 2; 3) any contraindication for walking, physical limitation to gait (orthopaedic or of other structural causes) that compromises physical activity, or other condition potentially interfering with the active treatment (e.g. severe arthritis or severe musculoskeletal pain associated with walking); 4) evidence of neurodegenerative disease (of aetiology other than vascular), severe mental disorder (e.g. major depressive episode or psychosis) or medical disease which could significantly interfere with the subjects’ participation or with their quality of life (e.g. cancer, congestive heart failure, or unstable angina).

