### Accelerometry assessment

The physical activity (PA) time of each participant is assessed by accelerometry (ActiGraph, GT3X+ model). The accelerometer is a device that measures the acceleration of normal human movements, ignoring high-frequency vibrations associated with mechanical equipment. All participants are asked to wear the accelerometer on the right hip, close to the iliac crest, for a week. The device activation, download, and processing is performed using Actilife v.6.13.3 software (ActiGraph, Fort Walton Beach, FL, USA). The devices are activated on the first day before the interview and data are recorded using the raw mode with a 30-Hz frequency and posteriorly downloaded into 15-s epochs.

A valid day is defined as having 600 min (10 h) or more of monitor wear and all participants with at least 3 valid days (including 1 weekend day) are included in the analyses. Accelerometer counts ≥ 100 counts per minute (cpm) are classified as PA with additional separation into light intensity (100–2019 cpm) and moderate-to-vigorous intensity (≥ 2020 cpm) [64, 65]. There are no cut-offs for the sedentary time using the three-axial information from this new generation Actigraph GT3X+ accelerometer; therefore, we used the previous cut-offs which are based on the vertical axis only. Compliance with PA recommendations for public health is assessed according to the WHO recommendations (adults: 150 min/week of at least moderate-to-vigorous intensity defined as ≥ 21.4 min/day).

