### Run-in period and follow up assessments

The use of a pre-randomisation run-in period aims to ensure the engagement and adherence of subjects and to reduce bias associated with different levels of knowledge concerning expected benefits of the intervention. Over 4 weeks there is an educational group session, where the structure of the study, the benefits of physical activity, and the accelerometry report are explained.

Follow-up assessments will be conducted by clinicians (neurologist, neuropsychologist, and exercise physiologist not involved in the intervention sessions and blinded to the arm).

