### Randomisation and masking

After the 4-week run-in period, research personnel not involved in the recruitment, assessment, or intervention are responsible for managing the randomisation process using a statistical program. The randomisation sequence is generated by R software [69]. Participants are randomly assigned (1:1) to either the intervention group (IG) or to the best practice usual care group (CG), stratified by gender.

All follow-up assessments (physical, neuropsychological, and clinical diagnosis), and also the neuroradiological evaluation, are blinded to treatment allocation, as well as in the data set registry.

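### The primary model's covariate list leaves out baseline physical activity, although the trial measures it before randomisation, sets no entry limit on it, and by its own hypothesis expects it to affect cognition

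*Protocol article*

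**What the plan says.** All of this is in the protocol article.

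- **Entry.** The Inclusion criteria open with "Participants are included if they are 18 years and older and fulfil the following criteria" and go on to consent, language, literacy, an informant and the clinical and functional criteria. Habitual activity is not mentioned. The activity-related exclusion covers people who cannot exercise: "any contraindication for walking, physical limitation to gait (orthopaedic or of other structural causes) that compromises physical activity". Under Recruitment and study setting, "participants can be self-presenting, as the study was advertised in public spaces".
- **Control arm.** In the Design section, usual-care participants are told that "they are allowed to perform physical activity by self-initiative, although supervised physical intervention is not allowed". The next statement on the matter is an expectation: "We do not expect to see high levels of physical activity in the usual care group since VCI is usually associated with a reduced initiative".
- **Measurement.** Accelerometry is done at baseline, 6 and 12 months (Assessments). The Design section places all planned assessments in the run-in, and the run-in has a group session "where the structure of the study, the benefits of physical activity, and the accelerometry report are explained". Baseline activity is therefore known before allocation. The Accelerometry assessment section also supplies a cut-off: "Compliance with PA recommendations for public health is assessed according to the WHO recommendations", that is 150 min/week or 21.4 min/day of moderate-to-vigorous activity.
- **Use.** Allocation is 1:1, "stratified by gender" only. The Data analysis section says that covariates are chosen because they are assumed to affect cognition over follow-up, and lists age, gender, education and baseline MoCA.

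**The concern.** The article states a principle for choosing covariates and then omits a variable that meets it. The trial's hypothesis, at the end of the Background, is that regular moderate activity improves cognition in this population. If so, activity at entry should be prognostic as well. It is also the baseline characteristic closest to what the intervention changes, and it is collected at no extra cost before randomisation.

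Three things are at stake. A chance imbalance in baseline activity between arms would go unadjusted. Any precision that the variable offers would be forgone. And if many entrants are already active, the arms may differ less in exposure than planned, with no pre-specified analysis in the article to show it.

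**Working it through.** **1. Does baseline activity enter anywhere?** Reading the sections side by side: eligibility, no; stratification, no (gender only); stated model, no (four other covariates). It is used for counselling, for monitoring activity in both arms and for describing compliance with the WHO recommendation.

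**2. Is overlap with the programme plausible?** The components under Experimental intervention and implementation add up per supervised session to:
- first phase: 10+5+15+5+15+5 = 55 min
- second phase: 10+5+20+5+15+5 = 60 min
- third phase: 10+5+25+5+20+5 = 70 min

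Two such sessions plus at least 30 min of unsupervised walking give 2×55+30 = 140, 2×60+30 = 150 and 2×70+30 = 170 min/week. Walking alone is 2×30+30 = 90, 2×35+30 = 100 and 2×45+30 = 120 min/week. Someone already at 150 min/week is near the programme's total volume. This compares minutes only, not content or supervision.

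**3. What could dilution cost?** Inputs from the Sample size section: control risk 31%, odds ratio 4, alpha 0.05 (two-sided assumed), 80% power, 117 per arm. The share f of participants with no benefit is not in the article and is assumed.

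*Reproducing the plan's figure.* Read as a benefit, an odds ratio of 4 gives odds (0.31/0.69)/4 = 0.1123, so an intervention risk of 0.1123/1.1123 = 10.1%. The pooled-variance formula for two proportions then needs 58 per arm (67 with continuity correction), not 117. Holding 31%, 117 per arm and 80% power fixed implies an intervention risk of about 15.6%. The mismatch is a separate matter. Here it means that two starting points must be carried.

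*Formulas.* Diluted intervention risk: p₂(f) = (1−f)·p₂ + f·0.31.

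Power = Φ{ [ (0.31−p₂(f)) − 1.96·√(2p̄(1−p̄)/117) ] / √([0.31·0.69 + p₂(f)(1−p₂(f))]/117) }, where p̄ is the mean of the two risks.

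*Example, f = 20%:*
- Implied effect: p₂(f) = 0.8×0.1559 + 0.2×0.31 = 0.1867. Power = Φ[(0.1233 − 1.96×0.0565)/0.0559] = Φ(0.22) ≈ 59%.
- Odds ratio of 4 taken literally: p₂(f) = 0.8×0.1010 + 0.2×0.31 = 0.1428. Power = Φ[(0.1672 − 1.96×0.0547)/0.0536] = Φ(1.12) ≈ 87%.

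| Assumed share with no benefit | Power, implied effect (31% vs 15.6%) | Power, literal odds ratio of 4 (31% vs 10.1%) |
|---|---|---|
| 0% | 80% | 98% |
| 10% | 70% | 94% |
| 20% | 59% | 87% |
| 30% | 47% | 75% |
| 40% | 36% | 61% |
| 50% | 26% | 45% |

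The direction is the same in both columns. The size depends on two things that the article does not settle: the true effect and the share of active entrants.

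**The case against.** A reader might infer that already-active entrants cannot gain, that the trial is therefore biased or badly underpowered, and that a null result could not be interpreted. The document supports none of these.

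- **No gain.** The Background says there are no data on the type, intensity or frequency of activity needed for lasting benefit. The supervised sessions progress in intensity and include resistance, balance and coordination work, which a hip-accelerometer total does not show a person to be doing already. Gaining less is plausible; gaining nothing is not shown.
- **Bias.** Randomisation protects the comparison. Chance imbalance in an unstratified covariate is ordinary sampling variation.
- **Power.** The low figures need both an unknown share of zero-benefit participants and an intervention risk of about 15.6% that the article does not state. With the odds ratio of 4 taken literally, power at a 20% share is still above the planned 80%.
- **Interpretation.** Activity is measured in both arms at all three visits, so a null result could be read against it, though the article pre-specifies no such reading.
- **The quoted expectation.** It concerns what controls will do during the trial, not who will volunteer.

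Broad entry against usual care is also a legitimate pragmatic choice, and subgroup or interaction analyses are often left to a statistical analysis plan, which is not shown here. Their absence from the article is not a fault.

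All of this stands. It does not answer the narrower point: the covariate list is stated in the article, and by the article's own rule baseline activity belongs on it.

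**Conclusion.** The point holds as an inexpensive improvement to the primary model, not as a design failure. The omission of baseline activity from eligibility, allocation and the stated covariates is plain from the text, and the trial's hypothesis places activity within its own rule for choosing covariates.

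The size of any dilution is unknown. The table is illustrative and rests on an assumed share, zero benefit in that share, a two-sided 0.05 test and a simple comparison of two proportions rather than the GEE model. Any dilution would come from open entry and permitted control activity. Adjusting or stratifying would not restore the contrast, so the tabulated losses are not what the fix would recover. What it offers is protection against chance imbalance, possibly some precision, and a planned way to read a null result.

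**What to change.** 1. In Data analysis, add baseline moderate-to-vigorous minutes per day as a continuous covariate in the primary GEE model, beside the four already listed.
2. State a simple rule for participants without 3 valid days including a weekend day, for example a missing-value indicator, so that everyone stays in the intention-to-treat analysis.
3. Pre-specify, as a supporting analysis, the arm-by-baseline-activity interaction together with the treatment effect among those below 21.4 min/day. If the statistical analysis plan already has this, a cross-reference is enough.
4. Optionally, if recruitment allows, stratify randomisation by that threshold as well as gender (2×2 = 4 cells). This would need a rule for invalid wear before allocation.

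The cost is small: no new data, one covariate and one supporting analysis. The downsides are some missing baseline accelerometry to handle and low power for the interaction, which should be reported as an estimate with its confidence interval and not used to claim or rule out effect modification.
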